### 6.1.1 Further Notes Regarding Inclusion and Exclusion Criteria for DGU Trauma Register:

Less severely and severely injured patients are often documented in the DGU Trauma Register. This not only increases the documentation effort but also complicates the comparability of results with other hospitals or over time. Therefore, since 2015, evaluations have only been conducted for the base collective and no longer for all documented patients.

#### WIdO:

Since the coding guidelines of ICD-10GM (= International Statistical Classification of Diseases and Related Health Problems, German Modification) do not allow for coding of MAIS or ISS, the existing identification criteria based on medical expertise will first be revised. These will be operationalizable in secondary data through combinations of specific ICD-10GM codes, OPS codes (= Operation and Procedure Key, version 2019), and DRGs. The first hospitalized injury that meets the inclusion criteria will be considered the index stay of the insured. The three-year follow-up period starts with the discharge from the index stay.

## 6.2 Number of Study Participants

The following table (Tab. 4) shows the planned sample size:

**Tab. 4: Sample Size Planning**

| Study Part               | Sample Size (n=)                        |
|---------------------------------|------------------------------------------------|
| Prospective Cohort Study | 1000 severely and critically injured patients  |
| WIdO Data                | 33,000 severely and critically injured insured |
| DGU Trauma Register      | 29,345 (Base collective in 2019)               |

## **6.3 Sample Size Calculation**

### **6.3.1 Sample Size Calculation for Prospective Cohort Study**

As severe injuries can occur in different body regions, the present cohort is considered heterogeneous. Therefore, the cohort must be large enough to allow for analyses of patient- and injury-specific subgroups (for example, traumatic brain injury), as well as the examination of socioeconomic and psychosocial factors. With a total of  $n=1000$  evaluable cases (with complete follow-up), prevalences of 10% can be reported with an accuracy of  $\pm 2\%$  (95% confidence interval), prevalences of 20% with  $\pm 2.5\%$ , and prevalences of 50% with  $\pm 3\%$ . In subgroups of 300 cases, there is still an accuracy of  $\pm 3.5/4.5/5.5\%$  for the aforementioned prevalences.

For the multivariate analyses of risk factors, a number of 5-10 patients per factor with an “event” (in this case, work ability) should be available. If approximately 30% of patients have not resumed work, about 30 predictors could be investigated across the entire cohort, which seems sufficient.

It is assumed that the consent rate for participation in the study will be about 50% (Kaske, 2019), of which it is expected that 25-30% will not complete the follow-up. According to experience from the DGU Trauma Register, an average of 120 severely and critically injured patients ( $\text{MAIS} \geq 3$ ) are treated annually in a Level-1 trauma center in Germany. After accounting for deceased patients (approximately 10%), around 100 patients remain per year. With a participation rate of 50% ( $n=50$ ) and an assumed maximum lost-to-follow-up rate of 30% ( $n=35$ ), approximately 30 participating trauma centers will be necessary to obtain 1000 evaluable patient cases within a one-year inclusion phase. To estimate selection bias, the study clinics will maintain a screening log of potential study patients. Additionally, a comparison of patient characteristics with the overall cohort of the DGU Trauma Register will be made using the same inclusion criteria (representativeness). The study clinics will include DGU-certified trauma centers that treat at least 40 severely and critically injured patients annually according to the inclusion criteria of the DGU Trauma Register. Currently, 45 trauma centers have already expressed interest in participating as study clinics, treating 40-250 patients annually according to the inclusion criteria of this study, see cooperation partners. Thus, it can be expected that the target numbers will be achieved, possibly even in a shorter recruitment time.

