#### **7.1.2 Prospective Cohort Study**

All participating study clinics will receive at least two training sessions explaining the study and follow-up procedures in detail. The recruitment, administration, tracking, and follow-up throughout the entire study will be conducted by the respective study clinic, which will

receive a tiered compensation of up to €660.00 per patient based on the number of successfully documented follow-ups in the web-based study database. Documentation of all assessments will be conducted exclusively in a pseudonymized manner in the web-based study database. The assignment list will be managed by the respective study clinic for the included patients.

After obtaining informed consent for study participation, baseline data will be collected before discharge (clinical data, profession, situation before the accident – exact contents are based on the results of patient and expert interviews as described in Ethical Application 1, Qualitative Study Arm; further information can be found in the section on Data Collection).

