## 7.2 Statistical Analysis

- **Description of Progress:** All patients; description of the regaining of work ability (AF) and health-related quality of life over time (3 follow-up points; descriptive statistics).
- **Predictors for AF:** AF up to 18 months after trauma as a yes/no criterion; univariate and multivariate analysis (logistic regression) of possible predictors; classification of predictors into the categories: patient, profession, pre-hospital, clinic, post-acute therapy, presence of psychological problems (from QoL assessment at follow-up time).
- **Predictors for Time until AF:** Only patients with regaining AF: Time until AF as a dependent variable, Kaplan-Meier curves for description, Cox regression for multivariate analysis, predictors as above.
- **Health-related Quality of Life and PREMs:** Description at the 3 follow-up points, correlation with AF as subgroup comparisons at each measurement time.

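### The precision stated in Protocol 6.3.1 is simple-random-sample precision, although the 1000 cases come from about 30 clinics; it should be restated with a design effect

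*Protocol*

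**What the plan says.** Section 6.3.1 bases the cohort size partly on precision. With 1000 "evaluable cases (with complete follow-up), prevalences of 10% can be reported with an accuracy of" ±2% (95% confidence interval), and the corresponding figures are ±2.5% at 20% and ±3% at 50%. It continues: "In subgroups of 300 cases, there is still an accuracy of" ±3.5/4.5/5.5% for the same three prevalences. No design effect or ICC is mentioned.

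The same section then explains where the cases come from: "approximately 30 participating trauma centers will be necessary to obtain 1000 evaluable patient cases within a one-year inclusion phase". The 45 clinics that have expressed interest are described as "treating 40-250 patients annually according to the inclusion criteria of this study", so clinic sizes will differ. Section 7.1.2 adds: "The recruitment, administration, tracking, and follow-up throughout the entire study will be conducted by the respective study clinic".

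Section 7.2 names logistic regression for regaining work ability by 18 months and Cox regression for the time until then. For the predictors it gives a "classification of predictors into the categories: patient, profession, pre-hospital, clinic, post-acute therapy", plus psychological problems. It says nothing either way about how clinic enters these models.

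**The concern.** Patients of one clinic share its catchment area, acute care, discharge practice and follow-up staff. Their outcomes and ratings are therefore likely to be somewhat alike, and 1000 such patients carry less information about the wider population than 1000 drawn independently. A half-width that leaves this out is too small.

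The stated precision is one of the two statistical reasons given for the cohort size; the other is the number of events per predictor. It is also what readers will use to judge how far subgroup results can be trusted. The figure is printed in the protocol, so a later analysis plan that handles clinic well would still leave it uncorrected.

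The same correlation bears on the regression models. The project wants to find modifiable factors in care, and section 10 foresees results feeding into the certification of trauma centers and networks. If any factor examined differs mainly between clinics, the handling of clinic decides whether its standard error is right.

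**Working it through.** **Inputs from the Protocol.** n = 1000 evaluable cases (6.3.1; Tab. 4 gives "1000 severely and critically injured patients"); subgroup n = 300; prevalences 10, 20 and 50%; 95% confidence, taken as two-sided; about 30 clinics. Mean clinic size m = 1000/30 = 33.3. The protocol's own recruitment chain gives a similar number: 100 × 0.5 × 0.7 = 35 per clinic.

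**Assumptions.** The documents give neither an ICC nor a coefficient of variation (CV) of clinic size. The ICC is taken as 0.005 to 0.05, with equal clinic sizes unless stated.

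**Step 1: reproduce the stated figures.** Half-width = 1.96 × √(p(1−p)/n).

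| n | 10% | 20% | 50% | Stated |
|---|---|---|---|---|
| 1000 | 1.86 | 2.48 | 3.10 | 2 / 2.5 / 3 |
| 300 | 3.39 | 4.53 | 5.66 | 3.5 / 4.5 / 5.5 |

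Rounded to the nearest half point, all six agree. The arithmetic is correct, and the figures contain no design effect.

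**Step 2: add the design effect.** DEFF = 1 + (m−1) × ICC with m−1 = 32.3; effective n = 1000/DEFF; the half-width is multiplied by √DEFF. For example, at ICC 0.02, DEFF = 1 + 32.3 × 0.02 = 1.65 and the 50% half-width is 3.10 × √1.65 = 3.98.

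| ICC (assumed) | DEFF | Effective n | 10% | 20% | 50% |
|---|---|---|---|---|---|
| 0.005 | 1.16 | 861 | 2.00 | 2.67 | 3.34 |
| 0.01 | 1.32 | 756 | 2.14 | 2.85 | 3.56 |
| 0.02 | 1.65 | 607 | 2.39 | 3.18 | 3.98 |
| 0.05 | 2.62 | 382 | 3.01 | 4.01 | 5.01 |

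**Step 3: does rounding absorb it?** Allowing a quarter point above each stated value, the limit is passed at an ICC of about 0.014 (10%), 0.007 (20%) and 0.003 (50%).

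**Step 4: sensitivity.**
- Unequal clinics, DEFF = 1 + ((1+CV²)m − 1) × ICC, assumed CV 0.5: ±2.5/3.3/4.2% at ICC 0.02 and ±3.2/4.3/5.4% at ICC 0.05.
- 45 equal clinics (m = 22.2) at ICC 0.05: DEFF 2.06 and ±2.67/3.56/4.45%.
- Subgroup of 300 spread evenly over 30 clinics (m = 10): ±3.47/4.63/5.78% at ICC 0.005 and ±4.09/5.45/6.81% at ICC 0.05. The loss is smaller because fewer patients share a clinic.

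**Step 5: what clinic handling would change in a regression.** If clinic were left out, a predictor constant within clinic would have standard errors too small by √DEFF = 1.15, 1.28 and 1.62 at ICC 0.01, 0.02 and 0.05. The true level of a nominal 5% test is 2 × (1 − Φ(1.96/√DEFF)) = 8.8, 12.7 and 22.6%. For a predictor that varies within clinic, the inflation is roughly 1 + (m−1) × ICC of predictor × ICC of outcome. With an assumed predictor ICC of 0.1 and outcome ICCs of 0.02 and 0.05, this is 1.065 and 1.162, and the true level is about 5.8 and 6.9%.

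**The case against.** The strongest reply is that the size of the effect is assumed. At ICC 0.005 the half-widths are ±2.0/2.7/3.3%, close to those stated, and with 45 clinics the loss is smaller. The figures are rounded planning values in a non-interventional cohort with no precision threshold to meet, and the cohort size also rests on the events-per-predictor argument. All of this stands, and it limits the weight of the point. It does not make the printed figures right for a clinic sample.

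One could also treat the participating clinics as fixed, so that variation between them adds no uncertainty. That does not fit a study that section 2.3.2 calls population-based and that, under 6.3.1, will be compared with the trauma register for representativeness.

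A reader might go further and infer that the planned logistic and Cox models treat patients as independent, so that their confidence intervals are too narrow throughout. The documents do not support this. Section 7.2 names only the model families. A random intercept, a frailty term or a robust variance are all ways of fitting them, and the choice may properly be left to the analysis plan. Nor is it shown that clinic-level predictors are planned: in the list in 7.2, clinic stands between the pre-hospital phase and post-acute therapy and may simply mean patient-level variables from the acute stay. Section 7.1.5 collects such items patient by patient, and no clinic characteristic is named as a predictor.

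**Conclusion.** The point holds for the precision statement in 6.3.1. The stated half-widths assume independent patients, while the design samples through about 30 clinics that run their own recruitment and follow-up. With equal clinic sizes and an assumed ICC of 0.005 to 0.05, the whole-cohort half-widths are about ±2.0 to 3.0%, ±2.7 to 4.0% and ±3.3 to 5.0% at prevalences of 10, 20 and 50%. At the upper end, the whole cohort at 50% prevalence is only a little more precise than the ±5.5% stated for a subgroup of 300.

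For the regression models the conclusion is conditional, and no error in 7.2 is established. The true level of about 9 to 23% applies only to a predictor constant within clinic, only if clinic is left out, and only for an ICC of 0.01 to 0.05. For predictors that vary within clinic the effect is much smaller. It is still worth committing to the handling of clinic now, given the intended use of the results.

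**What to change.** In 6.3.1, label the present figures as simple-random-sample precision. Beside them, give the half-widths multiplied by √(1+(m−1)×ICC) for a stated ICC range such as 0.005 to 0.05, with a note that unequal clinic sizes widen them further. The cohort need not be enlarged.

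In 7.2, add a sentence that the logistic and Cox models account for clinic, either by a random intercept and a frailty term respectively, or by cluster-robust standard errors with a small-cluster correction for about 30 clinics. State that prevalences will be reported with cluster-robust intervals. It would also help to say whether the clinic category of predictors means patient-level acute-care variables or characteristics of the hospital.

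The cost is a few lines of text and code and a less favourable precision statement. No new patients or data items are needed: each clinic documents its own patients in the study database, so the clinic should already be identifiable there.

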## **4. Scientific Background**

In Germany, approximately 30,000 people suffer a severe trauma each year (annual reports of the “Trauma Register DGU”). In recent decades, significant progress in preclinical and clinical treatment has markedly reduced the mortality rate of severely injured patients (Ruchholtz et al., 2008). With increasing survival rates, the functional outcomes and health-related quality of life of these patients are becoming more important. Affected patients suffer from chronic pain, psychosomatic disorders, and unemployment (Simmel et al., 2010; Simmel et al., 2013), as well as increased post-traumatic morbidity (Bouillon et al., 1998; Holtslag et al., 2007; von Rüden et al., 2013).

The return of patients to the workforce is important to promote their quality of life and social participation and to reduce the socioeconomic burden on society due to disability. According to current data from the “Trauma Register DGU,” 60% of severely injured patients in Germany are of working age (18-65 years), and three-quarters are male. With a current legal retirement age of 67 years, disability can lead to a financial gap of several decades. The high unemployment rate after trauma is well-known. According to the Hannover Polytrauma Long-Term Study (HLPS) (Sittaro et al., 2007), an average of about 22% of patients who were previously able to work are unemployed. Another 16% have undergone retraining due to their

accident to maintain work ability, and 24% have been classified for early retirement due to the accident. According to a Dutch study, only 58.5% of the severely injured patients of working age who were followed up were able to engage in full-time employment 15 months after the trauma, and an additional 21.5% could only pursue part-time employment (Holtslag et al., 2007). According to data from a pilot study on outcome assessment, only about 30% of all severely injured patients in Germany are able to work again two years after an accident (Kamp et al., 2019).

Following predictors of clinical treatment for disability have already been identified: patient age, severity of injury, traumatic brain injury, duration of intensive medical treatment, psychological sequelae, subjective perception of the injury, and the patient's education level (Frink et al., 2014; Kaske et al., 2014).

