**Tab. 3: Inclusion and Exclusion Criteria**

| Study Part                      | Inclusion Criteria                                                                                                                                             | Exclusion Criteria                                                                                                                                                                                                                                                                                                                                                                                            |
|---------------------------------|----------------------------------------------------------------------------------------------------------------------------------------------------------------|---------------------------------------------------------------------------------------------------------------------------------------------------------------------------------------------------------------------------------------------------------------------------------------------------------------------------------------------------------------------------------------------------------------|
| Prospective Cohort Study | 
 
Severely injured patients of working age (18-55 years) with an injury severity of MAIS* <math>\geq 3</math>;
 
 | 
 
Patients who are not communicative after the acute phase (inclusion point) (Glasgow Outcome Score <math>< 3</math>)
 
Insufficient German language skills (at least B1 language level according to the European Reference Framework)
 
Patients after a suicide attempt
 
Patients without a permanent residence or residing abroad
 
 |
| DGU Trauma Register      | 
 
Admission of a patient via the emergency room with subsequent intensive therapy
 
                              | 
 
Patients with less severe injuries
 
                                                                                                                                                                                                                                                                                                                          |

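### The calculation behind about 30 centres takes no step for the 18-55 age limit; on the protocol's own 60% working-age figure, 30 average centres give about 630-810 evaluable cases, not 1000

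*Protocol*

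**What the plan says.** Section 6.3.1 of the protocol builds the number of centres as a chain. A Level-1 centre treats "an average of 120 severely and critically injured patients" per year, with MAIS of at least 3 as the only stated qualifier. Then: "After accounting for deceased patients (approximately 10%), around 100 patients remain per year". Half of these consent (50), and with the maximum assumed loss of 30% there are 35 evaluable cases per centre. The conclusion is that "approximately 30 participating trauma centers will be necessary to obtain 1000 evaluable patient cases within a one-year inclusion phase". Loss to follow-up is first given as a range: "of which it is expected that 25-30% will not complete the follow-up".

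Tab. 3 limits the cohort by age: "Severely injured patients of working age (18-55 years) with an injury severity of MAIS" of at least 3. It also excludes patients for outcome score, language, suicide attempt and residence. Section 4, citing the same trauma register, says that "60% of severely injured patients in Germany are of working age (18-65 years").

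Section 6.3.1 adds that 45 centres have expressed interest and treat 40-250 patients a year by this study's criteria. It expects the target to be met, possibly sooner than planned. Tab. 4 gives the sample size as "1000 severely and critically injured patients", without saying whether that means enrolled or evaluable.

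**The concern.** The chain removes deaths, refusals and losses but never moves from all severely injured patients to those whom the cohort can enrol. Age alone is a large step, because the protocol's own background figure leaves at least 40% of severely injured patients outside 18-55. If the 120 covers all ages, about 30 centres in one year do not produce the 1000 cases.

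That number carries the rest of section 6.3.1: the stated ±2/2.5/3% precision, the subgroups of 300, and 30 predictors on about 300 patients who have not resumed work. It also governs how many sites to open and for how long.

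**Working it through.** **Inputs.** From section 6.3.1: 120 per centre, 10% deaths, 50% consent, 25-30% loss, 30 centres, 45 interested centres. From section 4: 60% aged 18-65. The share aged 18-55 is not given; in the same population it cannot exceed the 18-65 share.

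**The protocol's own figure.** 120 × 0.9 = 108, taken as about 100. Then 100 × 0.5 × 0.7 = 35 per centre; 1000 / 35 = 28.6 centres; 30 × 35 = 1,050. The figure of about 30 reproduces, with no age step.

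**With an age step of 60%.** Evaluable per centre = survivors × 0.6 × 0.5 × (1 − loss). The last two rows let every death fall outside working age, so that 120 × 0.6 = 72 eligible patients all survive.

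| Base | Loss | Per centre | 30 centres | Centres for 1000 |
|---|---|---|---|---|
| 100 × 0.6 = 60 | 30% | 21.0 | 630 | 47.6 |
| 108 × 0.6 = 64.8 | 30% | 22.7 | 680 | 44.1 |
| 100 × 0.6 = 60 | 25% | 22.5 | 675 | 44.4 |
| 108 × 0.6 = 64.8 | 25% | 24.3 | 729 | 41.2 |
| 120 × 0.6 = 72 | 30% | 25.2 | 756 | 39.7 |
| 120 × 0.6 = 72 | 25% | 27.0 | 810 | 37.0 |

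Rounded up to whole centres, the need is 38-48. If the 18-55 share were 50% (an assumption) with proportional deaths, 30 centres would give 525-608. None of these figures deducts the other exclusions.

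**Share needed for 30 centres to suffice.** With proportional deaths: from 1000 / 1,215 = 82% (108 survivors, 25% loss) to 1000 / 1,050 = 95% (100 survivors, 30% loss). With all deaths outside the eligible ages: 1000 / (30 × 120 × 0.5 × 0.75) = 74%, or 1000 / (30 × 120 × 0.5 × 0.7) = 79%. All exceed 60%.

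**Precision.** The half-width is 1.96 × √(p(1 − p)/n).

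| n | p = 10% | p = 20% | p = 50% |
|---|---|---|---|
| 1000 | 1.86 | 2.48 | 3.10 |
| 810 | 2.07 | 2.76 | 3.44 |
| 630 | 2.34 | 3.12 | 3.90 |

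**Predictors.** With 30% not resuming work, 630 cases give 189 events, or 189 / 30 = 6.3 per predictor for 30 predictors. With 810 cases it is 243 events, or 8.1 per predictor. With 1000 it is 300, or 10.

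**45 centres at the same average.** At 60% with proportional deaths: 45 × 21.0 = 945 up to 45 × 24.3 = 1,094. In the limiting case for deaths: 45 × 25.2 = 1,134 to 45 × 27.0 = 1,215.

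**Enrolment for 1000 evaluable.** 1000 / 0.75 = 1,334 and 1000 / 0.70 = 1,429, rounded up.

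**The case against.** The best defence is the 45 interested centres. They are said to treat 40-250 patients a year by this study's own criteria, which include age, and section 6.4 says 50-250 by those criteria. If so, the target may be reached whatever the 30-centre chain shows. This stands in part: failure of the study is not shown. Neither is sufficiency, because no mean volume is given. The sentence before attributes the same minimum of 40 to the register's criteria, and section 9 repeats 40-250 without naming any criteria. With proportional deaths, 45 centres at the assumed average leave little or no reserve.

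The sponsor may also reply that the 120 was already limited to 18-55. The text does not say so, and its only qualifier is MAIS.

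Three stronger readings are tempting, and the protocol does not support them.

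- A reader might take 630-680 as a ceiling for 30 centres. That range uses 30% loss and proportional deaths. The protocol also allows 25% loss, and its 60% describes severely injured patients rather than survivors, so figures up to about 810 are compatible with it.
- A reader might infer that 30 predictors are no longer supportable. The protocol's rule is 5-10 events per factor, and 6.3 lies within it. What is lost is the upper end of that rule.
- A reader might take the 1000 in Tab. 4 as the number enrolled, which would leave 700-750 evaluable. The table carries no such label, section 6.3.1 defines 1000 as evaluable, and nothing says that recruitment closes at 1000 enrolled.

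**Conclusion.** The point holds for the centre calculation. As written, it does not describe the population that the cohort can enrol. If the 120 is for all ages, 30 average centres fall about 19-37% short of 1000 evaluable cases before the other exclusions. The loss of precision is modest for descriptive prevalences, at most about 0.8 percentage points wider at 50% (3.90 against 3.10 at n = 1000).

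This rests on two assumptions: that the 120 has no age limit, which is read from the text's silence, and that the register's 60% applies to patients with MAIS of at least 3 at these centres. Using 60% for 18-55 is generous, because the band it describes is ten years wider. Tab. 4 is a minor matter of a missing label.

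**What to change.** - State in section 6.3.1 whether the 120 is restricted to ages 18-55. If it is not, add the age step and the Tab. 3 exclusions to the chain. Then restate either the number of centres for 1000 evaluable cases (about 38-48 on the figures above, before the other exclusions) or the expected evaluable number from 30 centres, with matching precision and events per predictor.
- Reconcile the volume statements: at least 40 by register criteria, 40-250 by study criteria (section 6.3.1), 50-250 by study criteria (section 6.4). Rest the expectation of reaching the target, possibly sooner, on the 45 centres' actual eligible volumes.
- Label the 1000 in Tab. 4 as evaluable and give the matching enrolment target, about 1,334-1,429 at 25-30% loss.

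The cost is some restated text and figures in sections 6.2, 6.3.1 and 6.4, plus a request to the centres for age-restricted counts. The stated number of centres or the stated precision becomes less favourable.
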